## Abstract

**Background:**

Aortic dissection (AD) is a life-threatening cardiovascular emergency characterized by rapid onset and high mortality. While surgery intervention, the primary treatment, improves short-term survival, it frequently leads to postoperative complications including systemic inflammatory response syndrome, gastrointestinal dysfunction, and anxiety/depression. These complications may be exacerbated by dysregulation of the gut-brain axis (GBA). Transcutaneous auricular vagus nerve stimulation (taVNS) is a non-invasive neuromodulation technique known to exert anti-inflammatory, prokinetic, and neuroregulatory effects in various conditions; however, its application for managing postoperative complications in AD remains unexplored. This study aims to evaluate the efficacy and safety of taVNS in regulating the GBA among postoperative AD patients through a randomized controlled trial.

**Methods:**

This is a single-center, randomized, investigator-blinded, sham-controlled randomized controlled trial. A total of 50 patients aged 18–75 years with postoperative Stanford Type A or B AD will be enrolled and randomly assigned in a 1:1 ratio to either the active taVNS group or the sham control group. Both groups will receive standard postoperative care. The experimental group will additionally receive active taVNS targeting the vagus nerve-innervated auricular area (15 Hz, 200 μs pulse width), while the control group will receive sham stimulation at a non-vagus innervated site without electrical current. The intervention will be administered for 30 min, twice daily, over 7 consecutive days, with follow-up assessments continuing until 24 weeks post-surgery. Primary outcomes include changes in gut microbiota diversity/abundance and brain function (assessed via functional near-infrared spectroscopy). Secondary outcomes encompass inflammatory markers, plasma neurotransmitter levels, intestinal function recovery, and relevant psychometric scale scores. Safety will be monitored through vital signs, laboratory tests, and recording of any adverse events.

**Discussion:**

This study is the first to innovatively integrate taVNS with the GBA theory, investigating its multi-target mechanisms through a comprehensive set of biomarkers and clinical endpoints. If proven effective, taVNS could offer a safe and cost-effective non-pharmacological adjunctive therapy for managing postoperative complications in AD. Furthermore, the findings have the potential to elucidate the role of the GBA in the recovery trajectory of patients following major cardiovascular surgery.

**Trial Registration:**

Chinese Clinical Trial Registry (ChiCTR, http://www.chictr.org.cn), No. ChiCTR2500102345, Date: May 13, 2025.

## Introduction

1

Aortic dissection (AD) is a life-threatening cardiovascular emergency characterized by a tear in the aortic intima, leading to blood flow within the aortic wall and formation of a false lumen (1). AD is classified as Stanford Type A (involving the ascending aorta) or Type B (confined to the descending aorta). Untreated Type A AD carries a mortality rate exceeding 50% within 48 h (2, 3). The incidence of acute AD is approximately 1.9-fold higher in men than in women, with a male-to-female ratio of 2:1–3:1 for Stanford Type A AD (3). The pathophysiology of AD primarily involves structural abnormalities of the aortic wall, hemodynamic stress, and inflammatory activation (4–6). The gut-brain axis (GBA) offers a novel perspective for intervening in multi-system diseases. Gut microbiota dysbiosis is implicated in AD pathogenesis, exacerbating vascular inflammation and remodeling via the GBA (7). Furthermore, dysbiosis and impaired intestinal barrier function can amplify systemic inflammatory response syndrome (SIRS) through neural, immune, and endocrine pathways, adversely affecting cardiovascular and central nervous system function (8).

While surgery significantly improves short-term survival in AD, postoperative complications—including SIRS, gastrointestinal dysfunction, anxiety, and depression—remain major challenges that adversely impact long-term prognosis (9). These complications are closely linked to GBA dysregulation. Intestinal dysbiosis promotes vascular inflammation via neural, immune, and endocrine pathways, while gut barrier dysfunction fuels SIRS, creating a vicious cycle with neuropsychological impairment (10). Despite advances in acute AD management, effective long-term strategies are lacking. The critical postoperative status of AD patients in the ICU—with unstable vital signs, impaired consciousness, and polypharmacy—poses a major challenge for clinical research. Existing therapies often fail to concurrently address cardiovascular instability, inflammation, and quality of life, particularly in patients with comorbid psychological stress and intestinal dysfunction. Moreover, the impact of conventional treatments on the GBA is unknown, underscoring the need for novel interventions.

Transcutaneous auricular vagus nerve stimulation (taVNS) is a non-invasive technique that modulates autonomic nervous system activity, suppresses pro-inflammatory cytokine release, and improves intestinal and central neurotransmitter function by stimulating the auricular branch of the vagus nerve (11). However, its application in post-surgical AD patients remains unexplored. taVNS enhances vagal tone, mitigates SIRS, and provides cardioprotection (12). It also restores intestinal barrier integrity by modulating gut microbiota composition—increasing beneficial genera like *Bifidobacterium* and *Lactobacillus*—and reducing pathogenic metabolites (13). Additionally, taVNS alleviates bloating and constipation by enhancing vagal efferent signaling, which promotes gastrointestinal motility and digestive secretion (14). In AD patients, these effects could reduce gut-derived endotoxin absorption and lower systemic inflammation. Although gut microbiota dysregulation and GBA disorders are evident in AD, this field is still emerging. More foundational research is required to definitively link taVNS with GBA modulation post-AD and establish it as a therapeutic target.

Based on previous studies, taVNS offers the following advantages for intervening in postoperative complications of AD: ① Its non-invasive nature avoids the risks of invasive procedures, making it suitable for the long-term postoperative management of AD patients; ② It enables multi-target regulation of the autonomic nervous system, inflammatory response, and intestinal function; ④ Existing clinical trials show that taVNS has mild side effects, no serious complications, and high safety.

Therefore, we hypothesize that taVNS can ameliorate systemic inflammation, enhance intestinal and neurological recovery, stabilize hemodynamics, and reduce complications in postoperative AD patients by modulating the GBA. We have designed a randomized controlled trial to evaluate the clinical efficacy and mechanisms of taVNS, focusing on GBA regulation. This study is the first to investigate taVNS in AD patients, addressing the evidence gap for targeted GBA interventions after cardiovascular surgery.

## Objectives

2

This study aims to evaluate the efficacy and safety of taVNS on GBA-related outcomes in postoperative AD patients. Key endpoints include cardiovascular function, hemodynamics, inflammatory status, gut microbiota, neurotransmitter levels, psychological scores, and quality of life. Furthermore, we seek to provide evidence for the role of taVNS in regulating the GBA to mitigate postoperative complications in AD.

## Methods

3

### Design

3.1

This is a single-center, randomized, investigator-blinded, sham-controlled trial. The protocol was registered with the Chinese Clinical Trial Registry (ChiCTR2500102345) on 13 May 2025 and approved by the Ethics Committee of Guangdong Provincial Hospital of Traditional Chinese Medicine (Approval No. ZF2025-162-01) on 18 April 2025. The study will be conducted in accordance with the Declaration of Helsinki. A total of 50 eligible postoperative AD patients will be recruited from the hospital and randomized to receive either active taVNS or sham stimulation. The study flow is outlined in Figure 1, and the schedule of events is presented in Table 1.

**Figure 1 F1:**
[figure not shown]
Clinical trial flow chart.

**Table 1 T1:** Schedule of clinical trial index collection.

**Indicators**	**Screening period**	**Treatment period**			**Follow-up period**	
	**Visit 1 (days 1-7 before surgery)**	**Visit 2 (postoperative day 1, before intervention)**	**Visit 3 (daily monitoring for 1-7 days post-intervention)**	**Visit 4 (7 days post-intervention)**	**Visit 5 (4 weeks after surgery)**	**Visit 6 (24 weeks after surgery)**
General Information	✓					
Physical Examination	✓	✓	✓	✓	✓	✓
Written informed consent	✓					
Blood routine testduplicate	✓	✓		✓		
Liver function	✓	✓		✓		
Renal function	✓	✓		✓		
Coagulation function	✓	✓		✓		
Urine routine test	✓					
Urine pregnancy test in women of childbearing age	✓					
CTA of the Aorta	✓				✓	✓
Frequency of bowel sounds		✓	✓	✓		
The time of first flatus/defecation		✓	✓	✓		
GIDS		✓	✓	✓	✓	✓
HAMA		✓	✓	✓	✓	✓
HAMD		✓	✓	✓	✓	✓
SF-36		✓	✓	✓	✓	✓
PSQI		✓	✓	✓	✓	✓
IL-6		✓		✓	✓	✓
TNF-α		✓		✓	✓	✓
5-HT		✓		✓	✓	✓
BDNF		✓		✓	✓	✓
Gut Microbiota		✓		✓	✓	✓
BCI		✓		✓	✓	✓
NIRS		✓		✓	✓	✓
Adverse events	Record at any time					
Review of CRF	Review at any time					

GIDS, gastrointestinal dysfunction score in critically ill patients; HAMA, Hamilton anxiety scale; HAMD, Hamilton depression scale; SF-36, the short form 36 health survey; PSQI, Pittsburgh sleep quality index; IL-6, interleukin-6; TNF-α, tumor necrosis factor-α; 5-HT, 5-hydroxytryptamine; BDNF, brain-derived neurotrophic factor; BCI, brain-computer interface; NIRS, near infrared spectroscopy.

### Participants

3.2

#### Diagnostic criteria for AD

3.2.1

The diagnostic criteria for AD were established with reference to the *Thoracic Surgery Clinical Practice Guidelines on the Management of Type B Aortic Dissection* (STS/AATS, 2022) (15) and the *Guideline for the Treatment of Thoracic Aortic Dissection Type A* (jointly released by multiple German societies, 2022) (16). They are specified as follows: ① Typical symptoms: Sudden, severe tearing or ripping pain in the chest or back, which may radiate to the abdomen, lower extremities, or back; some patients may present with no obvious pain (e.g., those with Marfan syndrome). ② Typical signs: A systolic blood pressure difference of >20 mmHg between the two upper limbs; a diastolic murmur audible over the aortic valve area; disturbances of consciousness; or signs of organ malperfusion (e.g., oliguria, lower limb pallor). ③ Imaging examination: Computed tomography angiography confirms the diagnosis by revealing an aortic intimal tear and the formation of true and false lumens. ④ Stanford classification criteria: Type A: Dissection involves the ascending aorta; Type B: Dissection is confined to the descending aorta.

#### Inclusion criteria

3.2.2

① Patients with postoperative Stanford Type A or Type B AD who are hemodynamically stable;

② Aged 18–75 years (inclusive), regardless of gender;

③ Have voluntarily provided a signed written informed consent form.

Only subjects who meet all three criteria above are eligible for enrollment in this study.

#### Exclusion criteria

3.2.3

① Severe hepatic or renal dysfunction: estimated glomerular filtration rate < 30 mL/min/1.73 m^2^ or Child-Pugh Class C;

② History of major psychiatric or cognitive disorders;

③ Pregnancy, lactation, or a positive urine pregnancy test at screening;

④ Resting heart rate < 50 bpm or resting systolic blood pressure < 90 mmHg;

⑤ Severe active infections, autoimmune diseases, chronic gastrointestinal diseases, or use of antibiotics/probiotics within 4 weeks prior to enrollment;

⑥ Concurrent use of medications that significantly affect autonomic nervous function (e.g., beta-blockers, anticholinergic drugs);

⑦ Contraindications to taVNS, such as known skin allergy to electrode materials or active ear infection;

⑧ Considered by the investigator to be unsuitable for trial participation.

Subjects meeting any of the above criteria will be excluded.

#### Removal criteria

3.2.4

Enrolled subjects will be removed from the study if any of the following conditions are met: ① Poor compliance, defined as a taVNS intervention completion rate of < 80%, or explicit refusal to cooperate with study procedures; ② Missing key outcome data (e.g., inflammatory markers, gut microbiota data) that preclude efficacy assessment. Reasons for removal will be documented in detail, and the case report form (CRF) will be retained. Data from removed subjects will be excluded from the per-protocol efficacy analysis but included in the safety analysis if they received at least one taVNS intervention.

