#### Drop-out criteria

3.2.5

Investigator-determined withdrawal: ① Occurrence of a serious adverse event (SAE) leading to trial discontinuation based on investigator judgment; ② Development of a new severe intercurrent illness that may confound efficacy or safety assessments.

Subject-initiated withdrawal: ① Voluntary withdrawal from the trial for any reason; ② Loss to follow-up, defined as failing to receive the intervention or complete assessments for two consecutive scheduled visits despite attempts to make contact.

Handling of Drop-out Cases: ① The investigator will attempt to contact the subject to document the reason for dropout and the last intervention date, and to complete any feasible assessments; ② Subjects who dropout due to adverse events will receive appropriate clinical management; ③ All data from dropout cases will be preserved and included in the intent-to-treat (ITT) analysis.

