### Quality control

3.8

① Standardization of Personnel and Operations: All research staff will receive standardized training and must pass competency assessments to ensure consistent execution of taVNS procedures, scale evaluations, and biospecimen collection.

② Quality Control of Equipment and Testing: Standard Operating Procedures will be strictly adhered to. taVNS devices will be calibrated weekly, with stimulation intensity set to a perceptible but non-painful level. All laboratory assays will use approved reagents, and gut microbiota analysis will be conducted by an accredited third-party laboratory. Blood and stool specimens will be stored at −80 °C within one hour post-collection under unique study identifiers.

③ Data and Monitoring Management: Source data will be entered into the CRF and verified by two independent personnel. Independent monitors will audit ≥30% of cases bi-weekly to ensure data completeness and consistency across intervention records, laboratory results, and AE documentation.

④ Graded Handling of AEs: Grade 1 AEs will be managed on-site and reported within 24 h; Grade 2 AEs will lead to temporary intervention suspension with reporting within 72 h; Grade 3+ AEs will result in immediate intervention cessation and rescue measures, with reporting to the EC within 2 h. All study documents will be archived for 5 years to ensure traceability.

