#### Main statistical models

3.9.2

Mixed-effects models will serve as the core analytical framework to handle repeated measures collected at 1 day, 7 days, 4 weeks, and 24 weeks postoperatively. ① A linear mixed-effects model will be used for continuous outcomes, including gut microbiota indices (Shannon index, Bifidobacterium abundance), brain function parameters (fNIRS rCBF, EEG α-wave power), and biochemical markers (IL-6, TNF-α, 5-HT, and BDNF). ② A logistic mixed-effects model will be applied to binary outcomes, such as adverse events (SAE, skin allergy) and intestinal function recovery (first flatus within 48 h, first defecation within 72 h). ③ An ordinal logistic mixed-effects model will be used for ordinal outcomes, including scale scores (GIDS, HAMA, and HAMD).

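### Section 3.2.4 removes randomised patients from the study for low adherence or missing outcomes and does not say whether they stay in the ITT analysis

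*Protocol article*

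**What the plan says.** Section 3.2.4 (Removal criteria) opens: "Enrolled subjects will be removed from the study if any of the following conditions are met". The first condition is "Poor compliance, defined as a taVNS intervention completion rate of < 80%, or explicit refusal to cooperate with study procedures". The second is "Missing key outcome data (e.g., inflammatory markers, gut microbiota data) that preclude efficacy assessment". The section then fixes what happens to the data: "Data from removed subjects will be excluded from the per-protocol efficacy analysis but included in the safety analysis if they received at least one taVNS". It asks for the reason to be documented and the case report form kept. It mentions neither further assessments nor intention to treat.

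Section 3.2.5 (Drop-out criteria) covers withdrawal by the investigator, voluntary withdrawal for any reason, and loss to follow-up. For these patients feasible assessments are to be completed, and "All data from dropout cases will be preserved and included in the intent-to-treat (ITT) analysis". This is the article's only reference to an ITT analysis. The article does not name the primary analysis set.

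Section 3.9.3 plans multiple imputation of outcomes taken to be missing completely at random or at random. Section 3.9.2 makes mixed models of the repeated measures, day 1 included, the core analysis.

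**The concern.** Adherence and availability of outcomes become known only after treatment has started. Ending a patient's participation on such grounds gives up the protection of randomisation if the patients who leave differ in prognosis, or leave at different rates in the two arms.

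Both are plausible here. Section 3.8 states that "Grade 2 AEs will lead to temporary intervention suspension with reporting within 72 h", and the sham delivers no current, so suspensions caused by stimulation would be expected mainly in the active arm. Gut microbiota is a primary outcome that needs a stool sample, and patients with slow bowels are less able to give one. They are also among the patients whose complications the trial sets out to treat.

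An ordinary per-protocol exclusion would do no harm beside a full ITT analysis. The wording, however, takes the patient out of the study, and the article confirms ITT membership for the other class only.

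**Working it through.** **1. How little non-adherence triggers removal.** Section 3.5.3 gives two sessions a day for 7 days: 2 × 7 = 14. The threshold is 0.80 × 14 = 11.2. Twelve sessions (12/14 = 85.7%) pass and eleven (11/14 = 78.6%) fail. Three missed sessions, or 1.5 days, are enough.

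**2. What each class is promised.**

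| | Removed (3.2.4) | Drop-out (3.2.5) |
|---|---|---|
| Further assessments | not stated | any that are feasible |
| Per-protocol | excluded | not stated |
| Safety | included if treated at least once | not stated |
| ITT | not stated | included |

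**3. Overlap.** Refusing to cooperate is a removal reason; withdrawing voluntarily for any reason is a drop-out reason. One patient can meet both. Likewise, a patient who cannot be reached for the 4-week and 24-week visits meets the loss-to-follow-up definition and also lacks later outcome data. Which rule applies, and so whether ITT membership is stated, is left to the classifier.

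**4. Missing outcomes.** Section 3.9.3 keeps a patient with a missing outcome and imputes the value. Section 3.2.4 removes a patient when missing key data prevent efficacy assessment. The two can coexist if removal concerns only the per-protocol set. They conflict if it means leaving the study, because later values that could have been collected, and would inform the imputation, are then lost.

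**5. Sample-size allowance.** Section 3.3 states 22 per group and a 10% dropout rate: 44/0.9 = 48.9, so 49, rounded up to 50, or 25 per arm. Three removals in an arm leave 25 − 3 = 22, exactly the stated number, with nothing over for drop-outs. (The 22 is taken as stated. The usual formula with the same inputs gives 2 × [(1.96 + 0.84) × 5/3]² = 43.6, so 44 per group. That is a separate matter, and nothing here depends on it.)

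**6. Size of a possible bias, illustration only.** Take the planning SD of 5 and no true effect, and suppose that removed patients are not analysed. With removal fractions q_a (active) and q_s (sham), and correlation ρ between the tendency to be removed and outcome, the spurious difference is

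5 × ρ × [φ(z_a)/(1 − q_a) − φ(z_s)/(1 − q_s)],

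where φ is the standard normal density and z the normal quantile of q. The values of φ(z)/(1 − q) are 0.350 at 20%, 0.195 at 10% and 0.109 at 5%. The q and ρ below are assumptions; the documents give neither. The type I error is that of the nominal two-sided 5% test with 25 randomised per arm.

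| Removed, active vs sham | ρ | Shift (points) | Type I error |
|---|---|---|---|
| 10% vs 5% | 0.3 to 0.5 | 0.13 to 0.22 | 5.1% to 5.2% |
| 20% vs 5% | 0.3 to 0.5 | 0.36 to 0.60 | 5.7% to 6.8% |
| 20% vs 5% | 1 (extreme) | 1.21 | 12.5% |

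If exactly the worst 10% of one arm leave and nobody leaves the other, the shift is 5 × φ(1.2816)/0.9 = 0.97 points, about a third of the planning difference of 3. Equal rates with equal selection in both arms give no bias, only a loss of power.

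**The case against.** The best defence is that section 3.2.4 names only one efficacy exclusion, from the per-protocol analysis, and that this is legitimate. Section 3.2.5 shows that an ITT analysis exists, and a condensed article may leave full definitions of analysis sets to another document. This stands as far as it goes. A reader might infer that removed patients are barred from ITT; the text does not say so. But the article does not simply leave the matter open. It sets out two classes, takes one of them out of the study, and states ITT membership only for the other.

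Other tempting readings also go too far:

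- **Removal differs by arm.** This is plausible but not shown. The article gives no adverse event rates by arm and no length of suspension, and does not say that suspended sessions count as poor compliance.
- **The first stool sample is lost because of treatment.** Table 1 schedules it on postoperative day 1, before the intervention, so stimulation cannot cause its absence, and randomisation balances that absence in expectation. The 72 h limit in section 3.9.2 ("first defecation within 72 h") is an example of a binary outcome, not a rate of missing samples. Only later samples could be affected by treatment.
- **Any missing sample means removal.** The rule is limited to missing data that prevent efficacy assessment. One missing day-1 value need not do so in a mixed model that takes day 1 as a response.
- **Three removals break the sample-size allowance.** They leave exactly the stated 22 per arm.

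**Conclusion.** The point holds as a fault in a stated rule. Section 3.2.4 takes randomised patients out of the study on post-randomisation grounds, leaves their ITT status unstated, overlaps with the drop-out class, and fits poorly with the planned imputation. Followed literally, it ends follow-up selectively.

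The size of any bias cannot be derived from the documents. The 0.97 points is a worst case for one-sided loss of 10%, not an expected value. With moderate assumed correlations the shift is 0.13 to 0.60 points and the type I error stays below 7%. All these figures assume that removed patients go unanalysed, and they use an SD that section 3.3 attaches to an example outcome (a quality-of-life score or IL-6), not to microbiota. The case for change rests on the low cost of the repair and on the fact that outcomes never collected cannot be recovered at analysis.

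**What to change.** 1. In section 3.2.4, replace removal from the study by exclusion from the per-protocol set only.
2. State that all randomised patients are followed to 24 weeks, whatever their adherence, unless they withdraw consent.
3. Name the primary efficacy analysis as all randomised patients, analysed as randomised, with per-protocol as a sensitivity analysis. The overlap between the two classes then no longer affects the primary result.
4. Delete missing outcome data as a removal reason. Handle it by the mixed model and multiple imputation already planned, with day 1 kept as a response so that a missing baseline stool does not drop the patient.

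A pre-operative stool should not be offered as a substitute baseline: Table 1 schedules none at Visit 1, so it would be a new procedure.

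The cost is an amendment of wording and some extra effort to follow non-adherent patients. The statistical downside is that these patients dilute the estimated effect slightly.
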